### Data sources

The analysis will use NJR data from April 2012 to December 2023. Furthermore, this dataset will be linked to the NHS England HES-APC data to supplement patient information that is not collected by the NJR, including patient comorbidities and ethnicity. The HES-APC data available for linkage only extends to 31 March 2022; therefore, the linked data will be used for a subgroup analysis. Mortality outcomes will be collected by linking the NJR data to the Civil Registrations of Death dataset. If death occurs before the revision outcome, it will be used to censor patients.

The NJR commenced the collection of data on elbow replacement procedures in April 2012. It is mandatory for all NHS and private hospitals in England, Wales, Northern Ireland, the Isle of Man and the States of Guernsey to submit data on elbow replacement surgeries, including both primary and revision procedures, to the NJR.^26^ The NJR, the British Orthopaedic Trainee Association, the British Orthopaedic Association, British Elbow and Shoulder Society (BESS) and the Royal College of Surgeons of England audited the NJR dataset in England. The TER dataset exhibited a completeness rate of 94% and an accuracy rate of over 97%.^23^ The data collected by the NJR have undergone various changes since the onset of elbow data collection, and these changes are detailed in online supplemental file 1.

The HES-APC data will be linked to the NJR data using an established process that is routinely used by NJR and detailed in a previous publication.^27^ For procedures to be linked, the start date of the HES-APC hospital episode must be the same as or before the NJR operation date, and the NJR operation date must be before or on the same day as the end date of the HES-APC episode. Access to the data and data linkage is facilitated under NJR permissions as explained in the Ethics and dissemination section.

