		Comorbidities indices	HES-APC	ICD-10 codes on HES data	Continuous
	Implant-related factors	Cement type	NJR	Derived from the implant codes of submitted implants	Categorical
		Polyethylene type	NJR	Derived from the implant codes of submitted implants	Categorical
		Presence of anterior flange	NJR	Derived from the implant codes of submitted implants	Categorical
	Surgical-related factors	Funding type	NJR	Directly submitted to NJR	Categorical
		Hospital type	NJR	Indirectly derived from NJR data	Categorical
		Humeral bone grafting	NJR	Directly submitted to NJR	Categorical
		Ulnar bone grafting	NJR	Directly submitted to NJR	Categorical
		Intraoperative complications	NJR	Directly submitted to NJR	Categorical
		Surgical approach	NJR	Directly submitted to NJR	Categorical
		Region where TER was performed	NJR	Indirectly derived from NJR data	Categorical

ASA, American Society of Anaesthesiologists; BMI, Body Mass Index; HES-APC, Hospital Episode Statistics-Admitted Patient Care; ICD-10, International Classification of Diseases, 10th Revision; NJR, National Joint Registry; RHR, radial head replacement; TER, total elbow replacement.

It is important to highlight that both patients and healthcare professionals identified the volume of surgeries performed by specific surgeons and hospitals as an important potential prognostic factor that warrants further investigation. Although previous studies have explored the relationship between surgeon and hospital volume in relation to hip and shoulder replacements,^30 31^ the statistical modelling used in these analyses is complex and beyond the scope of this study. Therefore, a separate study should be conducted to examine this relationship in more detail.

The use of HES-APC data enables the investigation of comorbidities as potential prognostic factors for the first time. We will evaluate both the Charlson Comorbidity Index and the Elixhauser Comorbidity Index. The Elixhauser Comorbidity Index encompasses a wider range of comorbid conditions and is reported to more accurately predict inpatient mortality following orthopaedic surgery compared with the Charlson Comorbidity Index.^32^ However, both the NJR and HES-APC data lack information on specific conditions related to the elbow, such as stiffness, functional weakness and ulnar neuropathy. These conditions are considered important by healthcare professionals who participated in the survey and would require further investigation in a separate study using different datasets.

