The collection of TER procedures on the NJR was performed using the NJR data collection tool known as the Minimal Data Set (MDS). Since the start of TER data collection, there have been 4 MDS versions, V.5–V.8. In this analysis, categorical variables will be classified based on the categories stated in the latest MDS form (MDS V.8). The measurement of each prognostic factor, including the categories to be used, is summarised in tables2^4^.

**Table 2 T2:** How patient-related prognostic factors will be measured

Variable	Data used in primary analysis	Data used in planned sensitivity analysis
Age	Continuous: measured in years	Categorical: ≥60/<60
Sex	Categorical: male/female/indeterminate	No difference
BMI	Continuous	Categorical: underweight/normal/overweight/obese/morbidly obese^41^
Height	Continuous: measured in centimetres	No difference
Weight	Continuous: measured in kilograms	No difference
Dominant arm	Categorical: yes/noPatients with unknown category will be excluded	Categorical: yes/no
ASA	Categorical: ASA1–ASA5	No difference
Indication for surgery	Categorical: Trauma/elective. Acute trauma/inflammatory/trauma sequelae/osteoarthritis/other.	No difference
Socioeconomic status	Categorical: Index of multiple deprivation quintile (V.2015)	No difference
Ethnicity	Categorical: classification is based on the ONS group classification 6a^42^Asian (includes Asian British or Asian Welsh)/black (includes black British, black Welsh, Caribbean or African)/white/mixed or multiple ethnicity/other ethnic group	No difference
Comorbidities (diabetes)	Categorical: yes/no	No difference
Comorbidities (osteoporosis)	Categorical: yes/no	No difference
Comorbidities indices	Continuous: CCI with revised weightings developed by [name] and used by the Health and Social Care Information Centre as part of the SHMI. Elixhauser Comorbidity Index.	No difference

ASA, American Society of Anaesthesiologists; BMI, Body Mass Index; CCI, Charlson Comorbidity Index; ONS, Office for National Statistics; SHMI, Summary Hospital-level Mortality Indicator.

**Table 3 T3:** How implant-related prognostic factors will be measured

Variable	Data used in primary analysis	Data used in planned sensitivity analysis
Fixation type	Categorical: cemented/uncemented/hybrid	No difference
Implant linkage	Categorical: linked/unlinked	No difference
Implant type	Categorical: Coonrad-Morrey/discovery/latitude legacy/latitude EV/latitude hybrid/GSB III/MUTARS/Nexel/IBP	No difference

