If RHR was used	Categorical: yes/no	No difference
Implant stem substrate	Categorical: cobalt chrome/titanium/stainless steel	No difference
Anterior flange	Categorical: yes/no	No difference
Implant stem finish	Categorical: plasma-sprayed/PMMA-coated/beaded porous-coated	No difference
Polyethylene type	Categorical: UHMWPE/HXLPE/vitamin E-HXLPE	No difference
Cement type	Categorical: Low/medium/high viscosity Antibiotic-loaded/no antibiotics	No difference

EV, EVolution; GSB III, Gschwend-Scheier-Bähler III; HXLPE, highly cross-linked polyethylene; IBP, Instrumented Bone Preserving; MUTARS, Modular Universal Tumour and Revision System; PMMA, polymethylmethacrylate; RHR, radial head replacement; UHMWPE, ultra-high molecular weight polyethylene.

**Table 4 T4:** How surgical related prognostic factors will be measured

Variable	Data used in primary analysis	Data used in planned sensitivity analysis
Funding	Categorical: NHS/independent sector	No difference
Hospital type	Categorical: NHS/independent sector	No difference
Grade of primary surgeon	Categorical: consultant/other	Categorical: consultant/SpR/senior fellow/F1-ST2/specialty doctor/other
Region	Categorical: East of England/London/Midlands/North East and Yorkshire/North West/South East/South West	No difference
Year of surgery	Continuous/discrete: the year of surgery	No difference
Humeral bone grafting	Categorical: yes/no	No difference
Ulnar bone grafting	Categorical: yes/no	No difference
Approach	Categorical: posterior/lateral	No difference
Intraoperative complications	Categorical: none/bone penetration/fractures/neurovascular-related complication/other	Categorical: None/humeral shaft penetration/ulna shaft penetration/humerus fracture/ulna fracture/nerve injury/vascular injury/other. None/fracture or bone penetration/nerve injury/vascular injury/other.

F1, Foundation Year 1; NHS, The National Health Service; SpR, Specialist Registrar.

Most of the information pertaining to potential prognostic factors is directly submitted using the MDS forms. Additionally, several potential prognostic factors are indirectly inferred from this data, which are detailed below along with the method used to derive the data:

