#### Statistical modelling methods

Initially, the relationship between each potential prognostic factor and the failure of TER will be examined using univariable Cox regression methods. After that, we will investigate this relationship while adjusting for other prominent variables that may affect this association by using multivariable Cox regression modelling methods. Based on the results of our systematic review,^35^ we will adjust for age, sex and the indication for TER surgery.

Hazard ratios from univariable (ie, unadjusted) and multivariable (ie, adjusted) regression methods will be estimated for each prognostic factor. Flexible parametric models will be considered if the Cox proportional hazard assumptions are violated.^36^ For continuous predictors, non-linear associations between the outcome and predictors will be explored using fractional polynomial methods.

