#### Sample size

We plan to use the complete elbow dataset from the NJR for this analysis; therefore, no formal sample size calculation will be performed as the total sample size and the number of failures requiring revision have already been predetermined. We will refer to Schmoor’s sample size calculation guidance to determine the number of predictor parameters we can include in our regression modelling strategies while limiting the potential for overfitting.^37^ Based on our previous study using the NJR elbow dataset, which included all TERs between 1 April 2012 and 31 December 2022,^38^ we expect the dataset for the analysis to include more than 3891 TERs, with over 244 of them requiring revision.

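### Year of surgery is coded as the calendar year, a scale on which one-term fractional polynomials are straight lines and two-term ones only a nearly collinear quadratic

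*Protocol article*

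**What the plan says.** Under Statistical modelling methods the protocol article states: "For continuous predictors, non-linear associations between the outcome and predictors will be explored using fractional polynomial methods". It gives no degree, power set, origin or scaling.

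Table 4 gives the measurement of year of surgery as "Continuous/discrete: the year of surgery", and its sensitivity-analysis column lists no alternative. Data sources sets the range: "The analysis will use NJR data from April 2012 to December 2023". That is twelve calendar years, the first of them a part-year.

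The comorbidity indices are also continuous. Table 2 has "Continuous: CCI with revised weightings developed by" a named source, followed by the Elixhauser index, and the text says "We will evaluate both the Charlson Comorbidity Index and the Elixhauser Comorbidity Index". They come from the hospital-episode linkage, of which Data sources says "therefore, the linked data will be used for a subgroup analysis".

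On information, Sample size says "we expect the dataset for the analysis to include more than 3891 TERs, with over 244 of them requiring revision".

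**The concern.** A fractional polynomial bends only if the largest value of the variable is well above the smallest. For calendar year the ratio is 2023/2012 = 1.0055; for years numbered 1 to 12 it is 12. Dividing by a constant leaves the ratio unchanged, so only moving the origin helps.

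Year of surgery is a listed candidate factor, and plausible shapes include an early fall that levels off. If the method is applied to the year as Table 4 gives it, a linear fit could be reported although the check had little ability to show anything else. Age and BMI have a categorical sensitivity analysis as a second look; year and the comorbidity indices do not.

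**Working it through.** The plan gives no figure on this point, so there is none to reproduce. The check uses the standard powers −2, −1, −0.5, 0 (log), 0.5, 1, 2, 3.

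**1. One term on calendar year.** Write x = 2017.5 + d, with d from −5.5 to 5.5. To second order, the largest departure of x^p from the straight line joining its end points, as a share of its range, is

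|p − 1|/2 × (5.5² − 0.5²)/(11 × 2017.5) = |p − 1| × 0.0676%.

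This gives 0.20% for p = −2, 0.14% for p = 3 and 0.07% for log. Direct calculation agrees (0.2028%, 0.1352%, 0.0676%). The smallest absolute correlation between any two powers is 0.99999. On 1 to 12 it is 0.40, and departures from the line for the non-linear powers run from 14% to 71%.

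**2. Two terms on calendar year.** Powers 1 and 2 give a quadratic, and to this accuracy so does every other pair. One minus the correlation of x and x² is 2.9 × 10⁻⁷. Condition numbers after standardising run from 528 to 25,384. The fit is estimable once centred and scaled.

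**3. Size of the usual test.** The 3-df test of two terms against linear uses a critical value of 7.815. On calendar year only one direction (the quadratic) is available, so the true size is about P(χ²₁ > 7.815) = 0.005.

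**4. Fit to assumed shapes.** Best R² over the twelve years:

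| Shape | Linear | One term, calendar | Two terms, calendar | One term, 1–12 | Two terms, 1–12 |
|---|---|---|---|---|---|
| U | 0.000 | 0.000 | 1.000 | 0.312 | 1.000 |
| log(year − 2011) | 0.895 | 0.896 | 0.983 | 1.000 | 1.000 |
| Step at 2017 | 0.734 | 0.735 | 0.769 | 0.740 | 0.838 |
| Flat, then rising after 2018 | 0.754 | 0.755 | 0.982 | 0.970 | 0.985 |

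**5. Approximate power.** Noncentrality = 244 × Var(log hazard) × (R² of the polynomial − R² of linear). This assumes a hazard ratio of 2 between the lowest- and highest-risk years and revisions spread evenly over years. For two terms on calendar year it is 14.49 (U), 0.87 (log), 1.00 (step) and 3.23 (late rise).

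- Two terms, calendar year, nominal 3 df: 0.91, 0.11, 0.12, 0.29.
- The same with the single direction recognised, Φ(√ncp − √7.815): Φ(3.81 − 2.80) = 0.84, Φ(0.93 − 2.80) = 0.03, Φ(1.00 − 2.80) = 0.04, Φ(1.80 − 2.80) = 0.16.
- Two terms, 1 to 12, nominal 3 df (somewhat optimistic): 0.91, 0.12, 0.27, 0.30.
- One term, 1 to 12: 0.57, 0.18, 0.07, 0.42. On calendar year the formula returns the nominal 0.05, but the best power gains almost no deviance, so actual rejection is close to zero.

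**6. Simulated Cox fits** (3,900 replacements, about 230 to 325 revisions, 60 runs per shape, assumed log-shaped fall or four-year fall then plateau). One term against linear exceeded 3.84 in 0% of runs on calendar year and 58 to 65% on 1 to 12. Two terms against linear: 25 to 30% and 35 to 37%. The Monte Carlo standard error is about 6 percentage points: √(0.6 × 0.4/60) = 0.063.

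**7. Comorbidity indices.** At a score of 0, powers −2, −1, −0.5 and log are undefined: 4 of 8. On an assumed 0 to 20 score, R² of the log term with linear is 0.690, 0.865 or 0.979 when 0.1, 1 or 10 is added first. Powers 0.5, 2 and 3 need no shift and still bend (R² with linear 0.933, 0.932, 0.832).

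**The case against.** The strongest reply is that degree, origin and scaling are details a journal article leaves to the full analysis plan, and an analyst may well re-origin year unprompted. That stands as far as it goes: the article does not say that the raw number 2012 to 2023 enters a one-term fit, and the table's continuous/discrete wording leaves room for a discrete analysis. But the article does choose to state each factor's coding and the method, and as stated the two fit badly.

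A reader might infer that fractional polynomials cannot bend on calendar year at all. The documents do not support that. No degree is fixed, and two terms recover a U-shape completely.

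A reader might also infer that non-linearity in the comorbidity indices would be missed. That does not follow either: no score range is given, so zeros are an assumption, and the positive powers remain usable at zero.

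Three further points stand.

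- The log shape used above is itself a one-term curve under the proposed coding, which favours the recode.
- Part of the two-term loss is test calibration. A centred quadratic tested on 1 df, Φ(√ncp − 1.96), gives about 0.97, 0.15, 0.17 and 0.43, so the recode is not uniformly better than that alternative.
- Low power for the non-U shapes also reflects the number of revisions.

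**Conclusion.** The point holds as a minor, inexpensive improvement. On the coding in Table 4, one-term polynomials for year are linear in all but name. Two-term polynomials are a quadratic judged by a test with a true size near 0.5% instead of 5%. Under the usual test, power for log, step and plateau shapes is lower than on years coded 1 to 12; for a U-shape the loss is small.

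These two properties are arithmetic and need no assumption beyond the year entering untransformed. The power figures rest on assumed shapes, a hazard ratio of 2 in the approximations, evenly spread revisions and small simulations, so they show direction more than size.

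The comorbidity point is secondary. It is conditional on zero scores and confined to the linked data, and it concerns an unstated constant that would influence the fitted shape. Age, BMI, height and weight are strictly positive and raise no zero problem. The adjustment for age, sex and indication is not touched.

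**What to change.** In Table 4, state that year of surgery is coded as years since 2011 (1 to 12) before the fractional polynomial is fitted. The quadratic stays among the candidates and other shapes are added. The cost is a recode and one line of text.

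Two limits should be acknowledged. Power remains modest with about 244 revisions. The negative powers also lean on the part-year 2012: with power −2, the step from 2012 to 2013 takes (1 − 0.25)/(1 − 1/144) = 76% of the term's range, so a selected negative power should be checked for dependence on that year.

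For the comorbidity indices, set the rule for zeros in advance, for example an indicator for score 0 plus a fractional polynomial on positive scores, or a fixed stated shift. This is also one line of text; the indicator uses one extra parameter.

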#### Sample size

We plan to use the complete elbow dataset from the NJR for this analysis; therefore, no formal sample size calculation will be performed as the total sample size and the number of failures requiring revision have already been predetermined. We will refer to Schmoor’s sample size calculation guidance to determine the number of predictor parameters we can include in our regression modelling strategies while limiting the potential for overfitting.^37^ Based on our previous study using the NJR elbow dataset, which included all TERs between 1 April 2012 and 31 December 2022,^38^ we expect the dataset for the analysis to include more than 3891 TERs, with over 244 of them requiring revision.

#### Missing data

Most of the potential prognostic factors collected by the NJR are compulsory for hospitals to submit and so are unlikely to be missing. Body Mass Index (BMI) and hand dominance do not have to be reported to the NJR if the data are not available, and the collection of BMI for elbows only started with the use of MDS V.7. This is likely to lead to missing data for those two factors. The extent of missing data will be reported, and the likely reasons for missing data will be explored.

Due to the expected high degree of data completeness, it is intended that the primary analysis for each prognostic factor will be based on a complete case analysis. We will also explore the use of multiple imputations as sensitivity analyses, where appropriate. A multivariate multiple imputation model, which includes the TER failure outcome and other prognostic factors, will be implemented. This approach avoids excluding participants from the analysis and is an effective method of handling missing prognostic factor information.^36^

#### Sensitivity analysis

In the primary analysis, several potential prognostic factors—including age and BMI—will be analysed as continuous variables. In the sensitivity analysis, these factors will be treated as categorical variables. This approach is motivated by the use of categorical data in previous literature, allowing for comparison with past studies and the potential combination of results in meta-analyses.

In addition, other prognostic factors such as intraoperative complications, grade of primary surgeon, arm dominance and diabetes as comorbidity will be categorised differently in the sensitivity analysis compared with the primary analysis. The specific categories for the sensitivity analysis are listed in tables2^4^.

The HES-APC dataset includes only NHS-funded procedures. If a significant number of procedures are conducted in the independent sector and, therefore, cannot be linked with HES-APC, a sensitivity analysis will be performed to compare those included in HES-APC with those carried out in the independent sector.

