**Trial registration number:**

NCT06760585.

STRENGTHS AND LIMITATIONS OF THIS STUDYThis is a protocol for the first analysis of prognostic factors associated with total elbow replacement failure using the National Joint Registry (NJR) elbow dataset, which is the largest elbow registry worldwide.This analysis will follow the methodological advances in prognostic factor research as proposed by the PROGnosis RESearch Strategy. It will be reported in accordance with the REporting recommendations for tumour MARKer prognostic studies guidelines.This analysis may be limited by missing prognostic factor data from the NJR and incomplete data linkage with the Hospital Episode Statistics-Admitted Patient Care dataset, as only NHS-funded procedures are included in this dataset.

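### The HES-APC linkage check does not settle whether its comparison group is set by funding or by place of surgery, and it omits NHS-funded TERs that fail to match, so it addresses selection by sector only

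*Protocol article*

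**What the plan says.** The Sensitivity analysis section of the protocol article first states the entry rule: "The HES-APC dataset includes only NHS-funded procedures". The next sentence sets a condition, "If a significant number of procedures are conducted in the independent sector and, therefore, cannot be linked with HES-APC", and then the comparison: "a sensitivity analysis will be performed to compare those included in HES-APC with those carried out in the independent sector". The strengths and limitations box gives the same single cause for incomplete linkage, "as only NHS-funded procedures are included in this dataset".

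Table 1 lists funding type (submitted directly to the NJR) and "Hospital type" (derived indirectly) as separate factors. Table 4 gives both the same levels, "Categorical: NHS/independent sector".

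Two other sections describe further ways a TER can go unlinked. Under Data sources, the NJR operation date must fall within a HES-APC episode, and "The HES-APC data available for linkage only extends to 31 March 2022". Under Participants and eligibility criteria, HES-APC episodes with unusable identifiers, impossible dates or no known discharge date are dropped. The same section excludes surgery outside England from the whole analysis, so that is not a source of unlinked TERs.

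**The concern.** Ethnicity, diabetes, osteoporosis and the comorbidity indices come only from HES-APC, so every result on them comes from linked TERs. A reader needs to know whether those TERs resemble the eligible TERs that could have been linked but were not. The planned comparison is the only stated analysis aimed specifically at that question.

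Three features weaken it:

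- The stated reason for non-linkage is funding, but the group is described by place. With two variables sharing the label of independent sector, two analysts could build different groups from the same sentence.
- It covers one reason for non-linkage and passes over failed matches among NHS-funded TERs.
- Its trigger counts independent-sector procedures only, so failed matches among NHS-funded TERs in NHS hospitals would never set it off, however many there were.

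If TERs that fail to match differ in case mix or revision risk, the linked-cohort hazard ratios could be affected without the planned check showing it.

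**Working it through.** The plan has no figure to reproduce here. The check is to assign each kind of TER within the HES window (April 2012 to 31 March 2022) to the two planned groups, under each meaning of independent sector.

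| TER within the HES window | Linked? | Read as place | Read as funding |
|---|---|---|---|
| NHS-funded, NHS hospital, matched | Yes | Linked group | Linked group |
| NHS-funded, NHS hospital, no valid match | No | Neither | Neither |
| NHS-funded, independent hospital, matched | Yes | Both | Linked group |
| NHS-funded, independent hospital, no valid match | No | Independent group | Neither |
| Not NHS-funded, independent hospital | No | Independent group | Independent group |
| Not NHS-funded, NHS hospital | No | Neither | Independent group |

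The second row is omitted on both readings. The third row is the possible overlap, and it arises only on the place reading.

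**Effect of overlap, if it exists.** Let *f* be the share of independent-hospital TERs that are NHS-funded and linked. Let m_L be the mean of some characteristic among linked TERs and m_U its mean among the remaining independent-hospital TERs. If the overlapping cases resemble other linked cases, the independent-hospital mean is f·m_L + (1 − f)·m_U. The observed contrast is then (1 − f)(m_U − m_L). The documents do not give *f*. For assumed values of 0.25, 0.50 and 0.75, the contrast shrinks to 0.75, 0.50 and 0.25 of its true size. On the funding reading f = 0 and nothing is lost.

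**Effect of omitting failed matches.** Take the funding reading, which favours the plan. Let *p* be the share of in-window TERs that are not NHS-funded, and *u* the share of NHS-funded in-window TERs with no valid match. The part of the unlinked in-window TERs that the check covers is p / [p + (1 − p)u]. Neither *p* nor *u* is in the documents, so these are assumed values:

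| p | u = 0 | u = 0.03 | u = 0.06 | u = 0.10 |
|---|---|---|---|---|
| 0.01 | 100% | 25% | 14% | 9% |
| 0.03 | 100% | 51% | 34% | 24% |
| 0.05 | 100% | 64% | 47% | 34% |
| 0.10 | 100% | 79% | 65% | 53% |

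For example, p = 0.03 and u = 0.03 gives 0.03 / (0.03 + 0.97 × 0.03) = 0.03 / 0.0591 = 51%. The check is complete if every NHS-funded TER matches. Coverage falls quickly if even a few per cent do not, above all when the independent sector is small, which is also when the trigger is least likely to be met.

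**Dates.** The comparison has no date limit. "The analysis will use NJR data from April 2012 to December 2023", so independent-sector TERs after 31 March 2022 can enter their group while no TER after that date can enter the linked group. Sector would then be mixed with year of surgery and length of follow-up.

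**The case against.** The strongest reply is that the sentence should be read whole. It speaks of procedures that cannot be linked, it follows a statement about funding, and independent sector is also a level of the funding variable. On that reading the groups are linkable and unlinkable procedures, and they cannot overlap. This is a fair reading. A reader might infer from the place wording that the groups do overlap. The documents do not establish that, and overlap is only possible. The ambiguity itself remains.

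A reader might also infer that the check cannot reveal selection at all. That goes too far. With the group defined by funding, it would show selection by funding, the one structural cause the protocol names.

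A third tempting step is to count all TERs after the HES end date as a measure of the defect: 21 of 141 months, or 14.9%, about 633 of 4,253 TERs at an even 3,891/129 per month. That is not supported. The cut-off is disclosed and is given as the reason for calling the linked work a subgroup analysis. It truncates by calendar time and is not failed linkage. Independent-sector TERs after that date would also still fall in the comparison group.

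It can further be said that the Missing data section promises to report the extent of missing data and explore the reasons, and that the linked analysis is secondary. Both are true. But that section names BMI and hand dominance as the likely gaps, does not mention linkage, and promises no comparison of linked with unlinked TERs. The lack of a numerical threshold for the trigger is a detail that could sit in a fuller plan, and it is not the complaint. The complaint is that the trigger counts the wrong thing.

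**Conclusion.** The point holds in limited form. The stated comparison uses place wording for a funding criterion, leaves out NHS-funded TERs in NHS hospitals that fail to match within the HES window, and depends on a condition those cases cannot meet. It can inform on selection by sector, but not on selection into the linked cohort as a whole.

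The size cannot be stated. The article gives no in-window linkage rate, no independent-sector share and no count of NHS-funded TERs done in independent hospitals. The coverage and dilution figures above only illustrate assumed values, and in-window linkage failure may prove small. The results affected are those for ethnicity, diabetes, osteoporosis and the comorbidity indices. The primary NJR-only analysis is not touched.

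**What to change.** Replace the conditional comparison with an unconditional one:

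1. Define the sector split by the NJR funding variable, not by hospital type.
2. Restrict to eligible TERs performed up to 31 March 2022, and compare linked with all unlinked TERs. Divide the unlinked by reason: not NHS-funded, or NHS-funded without a valid match. Report the number in each.
3. Compare the groups on baseline NJR factors and on net failure. Revision is taken from the NJR and so is available for unlinked TERs too.
4. Refit the NJR-only model with age, sex and indication in the linked subset and in all eligible TERs to 31 March 2022, and set the hazard ratios side by side.
5. In the limitations, name failed matching alongside funding as a cause of incomplete linkage.

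The cost is a reworded paragraph and a few extra tables from data already held. If nearly all NHS-funded TERs prove to be linked, the tables will show that and support the linked analysis.
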